### Design

This is an assessor-blinded, two-arm, parallel-group, randomized controlled clinical trial formulated in accordance with the Consolidated Standards of Reporting Trials (CONSORT) 2010 guidelines (supplementary file 1). This protocol was written using the Standard Protocol Items: Recommendations for Interventional Trials (SPIRIT) guidelines, and the SPIRIT checklist is provided in supplementary file 2. Eighty participants will be recruited in eight groups. Groups will be randomly allocated to the intervention (*n* = 40) and control (*n* = 40) groups in blocks of 4 in a 1:1 ratio. All 80 participants will receive treatment-as-usual (TAU). Those subjects allocated to the intervention group will receive TAU but will complete NEAT in lieu of nonessential aspects of the TAU program that do not explicitly target neurocognitive function (e.g., culinary or legal education classes). Thus, both NEAT and TAU groups received similar amount (e.g., intensity, duration, frequency) of intervention. Self-report, interview-based, and neuroimaging assessments will be performed before (pre; week 0), during intervention (from week 1 to week 7), after the intervention period (post; week 8), and/or after a follow-up period (3, 6, 12 months; weeks 20, 32, 56, respectively). Interview-based assessments were conducted by a trained clinical practitioner blind to the allocation of participants. Figure 1 summarizes the full design of the trial in accordance with the CONSORT flow diagram.

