### Sample size calculation

With total enrollment of *N* = 80 and an estimated 20% attrition rate, we anticipate having complete data at our primary endpoint (post-treatment) for 32 subjects per group or 64 in total. Due to cluster randomization, the effective sample size will be *n* = (*mk*)/[1 + *ρ*(*m* − 1)] where *m*, *k*, *ρ* are the number of subjects per cluster, the number of clusters, and the intra-cluster correlation, respectively [24]; here, *k* = 4, and on average, *m*= 8 (80% of 10) per cluster. Considering a range of 0.05 to 0.3 for *ρ*, *n*_Eff_ will be somewhere between 10.3 and 23.7 per group. This effective sample size will provide a precision of *t*_*n*-1,1-*α/2*_/√*n* or 0.43–0.70, times standard deviation as margin of error at 95% confidence for a continuous measure (self-reported drug craving), and 80% power to detect large effect sizes (*d* = 0.83 to 1.3) for group differences in pre to post or pre to follow-up changes at a two-sided 5% significance of a 2-sample *t* test. While we may be underpowered to detect small to medium effects, the current pilot study will be crucial for informing the viability of the intervention and for estimating power for future, larger clinical trials.

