### Randomization and blinding

All consented participants will receive NEAT or other active, but non-essential regularly scheduled programming at WIR coinciding with the same timeframe. Randomization will be happening in the group level, and groups of 9–12 participants will be randomly allocated to intervention conditions (study arms). This randomization will be conducted in blocks of 4 groups. The randomization will be determined prior to enrolling any subjects using computer-generated allocations.

The randomization codes will be generated by a statistician not involved in enrollment or delivery of interventions and will be kept in a secure computer file with controlled access. The research staff involved in the conduct of interview-based assessments (e.g., MINI, PRISM-5) will be blinded to the intervention condition. Participants and all research staff are kept blind to their intervention condition until completion of all baseline assessments. However, due to the nature of the intervention, participants and research staff involved in providing interventions will not be kept blind to the interventions after completion of baseline assessments. Research investigators (who are unblinded) will be involved in both delivering the intervention and doing the data analysis; therefore, outcome analysis will not be blinded.

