**Fig. 2 Fig2:**
[figure not shown]
Dynamic model of craving (DCM). A neuroscience-informed conceptual framework to define the major cognitive targets in the dynamic response to drug-related or emotionally salient cues that can end up to drug-seeking and consumption behaviors. E, environment; A, attention, S, saliency processing; M, memory; I, interoception; Co, control; R, response

NEAT consists of 14 90-min group sessions, which will be led by two trained master’s level therapists or therapists-in-training (e.g., doctoral students in clinical psychology) supervised by a licensed clinical psychologist (RLA). Groups are led by therapists according to the session-by-session manual. All sessions will be audio-recorded to support supervision and fidelity of implementation. Cartoon-based treatment binders and brain planners are provided to all participants. As the intervention is designed to be delivered in the group therapy setting during the trial and also in future clinical use, clustering of the effect due to the group administration of the intervention is not accounted as a variable of interest.

Each session starts with a didactic, psychoeducation portion describing the concepts and skills of focus in each session. The session is followed by a written material with descriptions of the concepts/skills in verbal and pictorial (cartoon) formats. The session continues with practicing cognitive tasks/games relevant for each skill and ends with a discussion of how they can monitor and practice each skill in their everyday life. Besides the in-session components, subjects are provided with homework material to practice the learned objectives between sessions, including monitoring their use of various brain functions, implementing compensatory strategies, and completing additional cognitive exercises. They are also asked to complete aspects of the brain planner between each session, starting with the retrospective recording of events and slowly progressing towards prospective planning. NEAT will target the cognitive domains shown in Fig. 3 through the use of the following five components:

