### Statistical analysis

Categorical variables will be summarized by frequency and proportion, and continuous variables by mean and standard deviation (SD), or by median and inter-quartile range if the distribution, appeared skewed even after simple (e.g., log) transformations, for all participants and for participants in each treatment arm. Data normality will be evaluated by quantile-quantile (QQ) plot and Shapiro-Wilk test.

Treatment effects will be compared by the intention-to-treat (ITT) principle, i.e., all subjects who were randomized will be included in the final analysis, regardless of their adherence to any of the interventions. In order to detect changes in the variables recorded for the primary and secondary outcomes, mixed-effects model analyses will be performed using fixed-effects of time (pre-, post-intervention time points) as a within-subject factor and condition (intervention vs. control) as a between-subject factor; within-subject dependency will be captured by either random cluster and/or subject intercepts or within-subject correlation structure (e.g., 1st-order autoregressive or exponential power), whichever Akaike or Bayesian information criterion (AIC or BIC) favor. Mixed-effects models allow using all available observations and, without the need of imputation, provide unbiased estimates under the missing at random mechanism, a plausible assumption for randomized trials, and are known to be more powerful than any ad hoc imputation [59]. We include age and IQ as covariates. The inclusion of other covariates will be determined by AIC and BIC. Subgroup analyses will be conducted according to the baseline neuropsychological and fMRI characteristics. Significance level will be set at 0.05 level for the primary outcome and hypothesis; Bonferroni correction will be applied to all pre-post comparisons for all secondary outcomes, and Benjamini-Hochberg’s procedure to control false discovery rate at 5% level for all the exploratory analyses. For each outcome measure (primary, secondary, and exploratory), effect sizes of Cohen’s *d* and *f* will be computed. The effect sizes, along with the attrition rate at each time point, can be used to guide future study design.

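### The primary model leaves group clustering of the pre-post change out of the craving test: at the protocol's own planning ICCs of 0.05 to 0.3, the nominal 5% test has a type I error of about 9% to 28%

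*Protocol article*

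**What the plan says.** **Design.** Under Design: "Eighty participants will be recruited in eight groups", allocated "in blocks of 4 in a 1:1 ratio". Under Randomization and blinding: "Randomization will be happening in the group level, and groups of 9–12 participants will be randomly allocated to intervention conditions". That gives four clusters per arm.

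**Sample size calculation.** "Due to cluster randomization, the effective sample size will be" *mk*/[1 + ρ(*m* − 1)], with *m* = 8, *k* = 4 per arm and ρ from 0.05 to 0.3. The resulting detectable effects are stated for differences in change from pre to post or to follow-up, so the discount is applied to the change.

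**Statistical analysis.** The mixed model has fixed effects of time and condition. The primary outcome is a change, so the test is the time-by-condition contrast, although the interaction is not written out. Within-subject dependency is to be "captured by either random cluster and/or subject intercepts or within-subject correlation structure", "whichever Akaike or Bayesian information criterion (AIC or BIC) favor". The primary outcome is tested at 0.05.

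**Active intervention.** The text after Figure 2 says that "clustering of the effect due to the group administration of the intervention is not accounted as a variable of interest", because NEAT is meant for group delivery in practice too.

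**The concern.** The unit of randomisation is the group, and the sample size section allows for women in the same group changing alike. The analysis section allows for this weakly, in two respects.

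- **The term is optional.** A fit criterion decides whether the groups appear at all. Under the correlation-structure option they do not.
- **The term is of the wrong kind.** Groups may enter only as a random intercept, which describes groups that differ in level. The primary test concerns change, and no listed term lets groups differ in change.

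At stake is the standard error of the primary contrast. If it is too small, p < 0.05 for craving does not carry a 5% error rate. The same model serves the secondary outcomes, so their Bonferroni-adjusted tests would start from p-values that are too small.

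**Working it through.** **1. The plan's own figures reproduce.** Inputs from Sample size calculation: *m* = 8, *k* = 4 per arm, so *mk* = 32.

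| | ICC 0.05 | ICC 0.3 |
|---|---|---|
| Design effect, 1 + 7ρ | 1.35 | 3.10 |
| Effective n per arm, 32/design effect | 23.70 | 10.32 |
| Margin of error, t/√n | 0.425 | 0.700 |
| d at 80% power, 2n − 2 df | 0.832 | 1.301 |

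These match the stated 23.7 and 10.3, 0.43 and 0.70, and 0.83 and 1.3.

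**2. Why the intercept does not help.** Write the outcome for subject *i* in group *j* at time *t* as fixed part + u_j + s_ij + e_ijt, with u_j the group intercept and s_ij the subject intercept. The change is fixed part + (e_ij2 − e_ij1). Both intercepts drop out, so the model's variance for the arm difference in mean change is 2σ²/(*mk*), where σ² is the variance of the change. If changes within a group have correlation ρ, the true variance is 2σ²[1 + (*m* − 1)ρ]/(*mk*). The model is short by exactly the design effect used for planning. In one fitted example with cluster and subject intercepts, the standard error was 0.2067, equal to that of the simple change-score test; the cluster-based standard error was 0.401.

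**3. Size of the error, in closed form.** Type I error ≈ 2[1 − Φ(1.96/√design effect)].

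- ICC 0.05: 1.96/√1.35 = 1.687, giving 9.2%.
- ICC 0.3: 1.96/√3.10 = 1.113, giving 26.6%.

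**4. Size of the error, by simulation.** 200,000 null trials per ICC, eight clusters of eight:

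| ICC of the change | Clustering ignored | t test on 8 cluster means, 6 df |
|---|---|---|
| 0 | 4.9% | 5.0% |
| 0.05 | 9.2% | 4.9% |
| 0.1 | 13.4% | 5.0% |
| 0.2 | 21.5% | 5.1% |
| 0.3 | 28.0% | 5.0% |

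**5. The listed mixed models, fitted directly.** 600 null trials per scenario by REML, with 10 women per group at baseline, 8 at follow-up and an assumed pre-post correlation of 0.5.

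| Model | ICC 0.05 | ICC 0.3 |
|---|---|---|
| Subject intercept, or cluster plus subject intercepts | 9.3–9.5% | 29.7–30.5% |
| Chosen by AIC or BIC | 9.3–9.5% | 29.5–30.5% |
| Cluster intercept only | about 4–6% | about 16–22% |

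With 600 trials, the Monte Carlo standard error near 30% is √(0.3 × 0.7/600) = 1.9 points, so this agrees with step 4. Without clustering at baseline, AIC kept a cluster term in about 3% of trials and BIC in under 1%. In the scenarios with baseline clustering they kept it in 73–80% and 59–66%. The error rate was the same either way.

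**6. If the right term were offered but selected.** Suppose a cluster effect on the change were a candidate, kept or dropped by AIC or BIC under REML. It is kept in 7–19% of trials at ICC 0.05. At ICC 0.3, AIC keeps it in 81% and BIC in 68%. The type I error after selection is still about 8% to 13%.

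**7. Power on 6 df.** With noncentrality d√(n/2) and 8 − 2 = 6 df:

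- ICC 0.05: d = 0.832 has 66.7% power, and 80% needs d = 0.98.
- ICC 0.3: d = 1.301 has 69.4% power, and 80% needs d = 1.48.

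**The case against.** **The 9% to 28% is conditional.** The protocol offers 0.05 to 0.3 as a range to consider, not as an estimate. A reader might infer that the error rate is inflated whatever happens; the document does not support that. At an ICC of zero for the change the test holds 5%. This stands, and the claim is limited accordingly.

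**The criteria do not always discard clustering.** A reader might infer that AIC and BIC usually drop a real group effect when there are only eight groups. For an effect on the change, that is so at an ICC of about 0.1 or below; at 0.3 they usually keep it. This does not rescue the plan, because the term actually on offer is an intercept.

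**The sentence on group administration is ambiguous.** It might be read as a decision to leave clustering out of the analysis. It stands in the description of the intervention and says only that clustering is not of interest. Clustering may be a nuisance and still be modelled, and the analysis section does permit a cluster term. The sentence needs clarifying and proves nothing by itself.

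**The cancellation is not universal.** It needs a subject effect in the model. A cluster-only intercept gives other rates, but its availability did not change the error of the selected model at the assumed pre-post correlation of 0.5.

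**Coinciding correlation structures are harmless.** With two time points several of the listed structures are the same; this does not affect the error rate.

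**It is a pilot in a condensed article.** A larger confirmatory trial is foreseen, which limits the consequences. But the article sets a 0.05 test on craving and itself states the random structure and the selection rule, so this is a stated choice and not a detail left to another document.

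**Conclusion.** The point holds in this form: groups are randomised and the sample size expects their members to change alike, but no listed model with a subject effect lets that clustering into the standard error of the primary contrast. The nominal 5% test then has a type I error of about 9% at an ICC of 0.05, rising to about 28% at 0.3.

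This rests on the protocol's planning ICC applying to the change, as its sample size section applies it, and on eight clusters of eight. The result for AIC/BIC-selected models also rests on the assumed pre-post correlation of 0.5. Making a cluster effect on the change available would not be enough if AIC or BIC still decided whether to keep it.

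**What to change.** **Statistical analysis.** Fix the random structure in advance and keep it whatever AIC or BIC says. Either of these would do:

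- a mixed model with a subject intercept and a random cluster-by-time effect (or a baseline-adjusted model of the post value with a random cluster intercept), tested with Kenward-Roger or Satterthwaite degrees of freedom; or
- a t test on the eight covariate-adjusted cluster means, on 6 df.

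Name one as primary. They are equivalent only with balanced clusters and a positive estimate of the cluster variance. Groups of 9–12 with dropout will not be balanced, and at an ICC of 0.05 the REML cluster variance was zero in 35% of simulated trials, so 6 df is not assured under the mixed model.

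**Active intervention.** Reword the sentence on group administration to agree with the sample size section: clustering may be a nuisance, but it must enter the standard error.

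**Sample size calculation.** Restate the detectable effects on 6 df: d of about 0.98 to 1.48 for 80% power, or about 67% to 69% power for the present 0.83 to 1.3.

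**Cost.** No new data. The price is wider intervals and a less favourable power statement.

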Numerous cognitive rehabilitation programs have been developed to focus on compensatory strategies and restorative exercises for NCDs associated with traumatic brain injuries [17], stroke [18], multiple sclerosis [19], and schizophrenia [20]. These programs have consistently been found to improve functioning and long-term outcomes for these groups of patients. There have been a few preliminary attempts to transplant cognitive rehabilitation programs for use with substance use populations, providing initial evidence that such programs could be beneficial. However, these programs did not explicitly link the cognitive rehabilitation modules to the processes involved in addiction and recovery. There is potential value in clarifying how such strategies may relate to the current neuroscientific understanding of addiction and recovery, as well as the co-occurring symptoms often experienced.

The present pilot study aims to characterize the clinical potential for an intervention targeting NCDs in OUDs and MUDs by enhancing awareness and use of neurocognitive skills in the context of substance use recovery. This aim will be accomplished by randomizing subjects who are already enrolled in substance use treatment to complete a novel “Neurocognitive Empowerment for Addiction Treatment” (NEAT) program or treatment-as-usual intervention. NEAT is novel in (a) its use of cartoons, brain awareness games, and real-life scenarios to ensure it is interactive and engaging; (b) its focus on the role of neurocognitive deficits in recovery from substance use and co-occurring mental health symptomatology; and (c) its incorporation of neuroscience findings specific to substance use.

The primary outcome in this trial is “change in self-reported drug craving from baseline to after intervention using the Obsessive Compulsive Drug Use Scale (total score) [21]. Secondary outcome is the mean change in self-report subjective cognitive functioning from baseline to after intervention using PROMIS Cog Abilities [22] and PROMIS Cog General measures [22]. Exploratory outcomes include additional psychological, neurocognitive, and structural and functional neuroimaging measures and are available on ClinicalTrials.gov. We hypothesis that as compared to the active control, the NEAT program will be associated with the following:

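### Effect modification by naturally continuous baseline neuropsychological and fMRI measures is planned as subgroup analyses; a continuous arm-by-measure interaction would use the same data better (minor, exploratory)

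*Protocol article*

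**What the plan says.** The only statement on effect modification is one sentence in the Statistical analysis section of the protocol article: "Subgroup analyses will be conducted according to the baseline neuropsychological and fMRI characteristics". It gives no cut-point, number of categories or interaction term. The same section applies Benjamini-Hochberg control of the false discovery rate at 5% to all exploratory analyses.

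Table 1 lists the candidate measures. The neuropsychological ones are the NIH Toolbox battery, a gambling task, delay discounting and go/no-go tasks. The fMRI ones are resting state, monetary incentive delay, stop signal and drug cue reactivity. The article does not call them continuous, but scores and activation measures of this kind naturally are.

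On size, the Design section states: "Eighty participants will be recruited in eight groups", with groups allocated "in blocks of 4 in a 1:1 ratio". The Sample size calculation assumes "an estimated 20% attrition rate" and so expects complete data for "32 subjects per group or 64 in total". It concedes that "we may be underpowered to detect small to medium effects".

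**The concern.** Forming subgroups from a continuous score means choosing a cut-point for each measure. It treats women on the same side of the cut as alike, and compares treatment effects estimated in parts of an already small trial. A treatment-by-measure interaction with the score left continuous asks the same question with all the information.

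The question has some interest here. The Background describes the aim as characterising the "clinical potential for an intervention targeting NCDs in OUDs and MUDs", while the inclusion criteria do not require a measured deficit. Analyses by baseline cognition are therefore where the article could show whether women with lower cognitive scores gain more. What is at stake is how much these secondary results can tell the designers of a later trial, not the trial's main comparison.

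**Working it through.** **Inputs.** From the Design section and Sample size calculation: 80 women in 8 groups, 1:1, 20% attrition, hence m = 8 completers per group and k = 4 groups per arm; intra-cluster correlation (ICC) ρ = 0.05 to 0.3. Assumed, because the article does not give it: the way scores are categorised, a standard normal modifier, and a linear effect.

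**1. The plan's own figures reproduce.**
- Completers: 80 × 0.80 = 64, or 32 per arm.
- Effective n per arm = mk/[1 + ρ(m − 1)]: 32/1.35 = 23.7 and 32/3.1 = 10.3, as stated.
- Margin t/√n: 0.425 and 0.700 SD (stated 0.43 to 0.70).
- Detectable d at 80% power, two-sided 5%, from the noncentral t: 0.83 and 1.30 (stated 0.83 to 1.3).

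The article gives no figure for the subgroup analyses.

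**2. Information lost by categorising.** The share retained is Σ pⱼ·μⱼ², where pⱼ is the proportion in category j and μⱼ the mean of the standard normal modifier in it. For a median split μ = ±√(2/π), so the share retained is 2/π = 0.637.

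| Categories | Lost |
|---|---|
| Two, median split | 36.3% |
| Two, 1/3 v 2/3 | 40.5% |
| Two, 25% v 75% | 46.1% |
| Tertiles | 20.7% |
| Quartiles | 13.9% |
| Kept continuous | 0% |

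The median split is the least costly two-way cut, hence at least 36%. These percentages do not depend on the sample size.

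**3. Precision within one half, if scores are cut in two.** Completers per arm per half: 64/2/2 = 16, about 4 from each randomised group. Effective n per arm = 16/[1 + 3ρ]: 16/1.15 = 13.9 and 16/1.9 = 8.4. The 95% margin for the difference between arms is t·√(2/n):
- t on 2n − 2 df: 0.78 SD (ρ = 0.05) and 1.04 SD (ρ = 0.3).
- t on 6 df (8 groups less 2 arms): 2.447 × 0.379 = 0.93 SD and 2.447 × 0.487 = 1.19 SD.

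The range is therefore roughly 0.8 to 1.2 SD.

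**4. Power of the interaction test.** Simulation with 8 groups of 8, group fixed effects, a standard normal modifier and ICC 0.05 to 0.3; 3,000 trials per cell. Both tests held their 5% level (0.049 to 0.053 under the null).

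| True interaction (SD per SD) | Continuous | Median split |
|---|---|---|
| 0.2 | 11–13% | 9–10% |
| 0.3 | 19–24% | 14–17% |
| 0.4 | 34–40% | 23–28% |
| 0.6 | 59–72% | 42–51% |
| 0.7 | 73–85% | 52–64% |

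The continuous analysis is better in every row. Below about 0.4 SD per SD neither is adequate.

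**The case against.** The strongest reply is that the article fixes no dichotomy. It names the characteristics and leaves the method open; the word subgroup is sometimes used loosely for any analysis of effect modification; and definitions and cut-points commonly belong in an analysis plan that is not shown here. This stands as far as detail goes, and the absence of cut-points is no fault. But subgroup analysis is the only approach named, and an analysis plan that follows the article would inherit it. If the word was meant loosely, one clarifying sentence settles the matter.

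Several stronger readings are tempting, and the documents do not support them:

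- *The plan throws away over a third of the information, with 16 women per arm in each subgroup.* Both figures assume a two-way split that the article does not state. With tertiles or quartiles the loss is 21% or 14%, although each subgroup is then smaller still.
- *Cut-points will be searched until a subgroup appears.* Nothing in the text describes this, and the Benjamini-Hochberg procedure already covers all exploratory analyses.
- *This is the trial's own question.* The Study objectives and the seven listed hypotheses all concern NEAT itself or NEAT against control; none is about a moderator.

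It is also fair to say that the imprecision comes mainly from having 64 women. The article calls itself a pilot and admits low power, and a continuous analysis does not cure that. Finally, under intention to treat, up to 80 women may contribute to the mixed model; this would narrow the margins somewhat but leave the percentages lost unchanged.

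**Conclusion.** The point holds in conditional form, as a minor one. The article names subgroup analyses for measures that are naturally continuous, in a trial expecting about 64 completers in 8 groups. If the scores are cut in two, at least 36% of the information on a linear modifier is lost (about 21% with tertiles, 14% with quartiles), and the effect within a half-sample has a 95% margin of roughly 0.8 to 1.2 SD. The percentages rest on a normal modifier with a linear effect. The margin rests on an equal split spread evenly over the randomised groups and on the article's own ICC range.

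A reader might infer that the plan is committed to losing over a third of the information; it is not, because the method of forming subgroups is not stated. The analyses are most naturally read as exploratory, and the primary outcome, its significance level and its model are untouched.

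**What to change.** Replace the subgroup sentence in the Statistical analysis section with wording such as:

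> Effect modification by baseline neuropsychological and fMRI measures will be examined by the arm-by-baseline-measure interaction on the change in outcome, with the measure kept continuous and randomised group in the model. Estimates are reported with 95% intervals, without within-subgroup p-values, and fall under the Benjamini-Hochberg procedure already planned for exploratory analyses.

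This needs no new data, since every listed measure is already in the assessment plan. The one downside is that linearity in the modifier is assumed, so it should be checked graphically. The change improves the analysis but does not make it well powered for small to moderate interactions, and the report should say so.

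### Plain Bonferroni on the two secondary cognition scales is valid but needlessly conservative; Holm's step-down keeps the same family-wise error and can only reject more

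*Protocol article*

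**What the plan says.** The Background section of the protocol article defines the secondary endpoint: "Secondary outcome is the mean change in self-report subjective cognitive functioning from baseline to after intervention using PROMIS Cog Abilities", together with a second scale, PROMIS Cog General. The hypotheses that follow are framed against the active control, so the test of interest on each scale is the between-arm difference in change.

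The Statistical analysis section sets three tiers. For the primary outcome, "Significance level will be set at 0.05 level for the primary outcome and hypothesis". For the secondary tier, "Bonferroni correction will be applied to all pre-post comparisons for all secondary outcomes". Exploratory analyses use the Benjamini-Hochberg procedure.

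The Sample size calculation section gives power for one continuous measure only, "at a two-sided 5% significance of a 2-sample" t test, with "32 subjects per group or 64 in total" after "an estimated 20% attrition rate". It gives no power, expected effect or between-scale correlation for the secondary scales, and it concedes limited power for small to medium effects.

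**The concern.** Single-step Bonferroni compares both p-values with 0.05/2 = 0.025 whatever happens to the other. Once one scale has been rejected, only one hypothesis remains open, and family-wise control no longer requires the stricter threshold for it. Holm's procedure uses this fact; plain Bonferroni does not.

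The trial randomises only eight groups and has little power to spare. If NEAT affects both scales and the larger p-value falls between 0.025 and 0.05 while the smaller is below 0.025, the stated rule calls the second scale non-significant. Holm would reject it at the same error rate. What is at stake is efficiency on the secondary outcomes, not the validity of any conclusion.

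**Working it through.** **1. The article's own figures.** Inputs from the Sample size calculation section: m = 8 completers per cluster, k = 4 clusters per arm, intra-cluster correlation ρ from 0.05 to 0.3.

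- Effective n per arm = mk/[1 + ρ(m − 1)]. At ρ = 0.05: 32/1.35 = 23.7. At ρ = 0.3: 32/3.1 = 10.3.
- Margin of error = t(n−1, 0.975)/√n = 0.425 and 0.700 SD.
- Effect detectable with 80% power, two-sided 5%, from the noncentral t with 2n − 2 degrees of freedom (about 45 and 19): d = 0.83 and 1.30.

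All three agree with the published values, so the same t-test framework is used below.

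**2. Same error rate, more rejections.** With two scales, Holm tests the smaller p at 0.025 and, if that is rejected, the larger p at 0.05.

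- Both null hypotheses true: any false rejection needs the smaller p to be at most 0.025, which has probability at most 2 × 0.025 = 0.05.
- One null hypothesis true: rejecting it needs its own p to be at most 0.05, which has probability at most 0.05.

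Neither step uses the correlation between scales. Any result rejected by Bonferroni (p ≤ 0.025) is also rejected by Holm.

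**3. Size of the gain.** Bonferroni confirms both scales if both p < 0.025. Holm confirms both if the smaller p < 0.025 and the larger p < 0.05. Two correlated t statistics with equal true effects were simulated, each with 80% single-test power at 0.05. The equal effects, the 80% power and the correlations are assumptions. The row with 6 degrees of freedom (8 groups − 2 arms) is also an assumption, with the effect set to keep 80% power.

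Chance of confirming both, Bonferroni → Holm:

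| df | corr 0 | corr 0.5 | corr 0.8 | corr 0.95 |
|---|---|---|---|---|
| 45 (n_eff 23.7, d 0.83) | 50→63% (+13) | 56→67% (+11) | 62→71% (+9) | 66→73% (+7) |
| 19 (n_eff 10.3, d 1.3) | 48→63% (+14.5) | 55→67% (+12) | 60→70% (+10) | 65→72% (+7.5) |
| 6 (assumed) | 44→62% (+18.5) | 49→65% (+16) | 55→69% (+14) | 60→70% (+9.5) |

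**4. Other effect sizes, same t test.** At d = 0.5 the gain is 6 to 7.5 points with n_eff 23.7 and 2 to 4 points with n_eff 10.3. At d = 1.3 with n_eff 23.7 it is 1 to 2 points, because both rules are then close to full power.

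**5. Other measures of power.** The chance of rejecting at least one scale is the same under both rules, because both start by comparing the smaller p with 0.025 (for example 79% at correlation 0.8). Average power per scale is half the sum of the chances of rejecting at least one and of rejecting both. It therefore rises by half the gain above, for example from about 70% to 75% at correlation 0.8.

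**The case against.** Bonferroni is prespecified, standard and conservative. The three tiers are clearly laid out, nothing in the article contradicts them, and the primary test is untouched. This stands: the point is an improvement, not an error.

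The article does not make confirming both scales an aim. It states a single hypothesis on subjective cognitive functioning, and for that reading the two rules have identical power to find at least one scale positive. This also stands, and it limits the practical weight of the gain. Effect sizes will be reported for every outcome whatever its significance, and the authors already expect a larger confirmatory trial.

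Bonferroni has simple matching simultaneous intervals and Holm does not. In a pilot meant to inform later designs, that is a real cost, though a small one, since ordinary 95% intervals serve that purpose.

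Two stronger readings are tempting and are not supported:

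- A reader might take a loss of 9 to 16 points as a fixed property of this trial. It is not. The range needs 80% power on each secondary scale, a correlation of 0.5 to 0.8 and, for its upper end, 6 degrees of freedom. The article gives none of these for the secondary scales. Stronger overlap between the scales shrinks the gain.
- A reader might infer from the mention of all pre-post comparisons that changes within each arm are also counted, giving four tests at 0.0125. The hypotheses are between-arm, and the phrase may simply separate the post-intervention endpoint from the later follow-ups. The exact count of tests is a detail an article can leave to the analysis plan.

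**Conclusion.** The point holds as a cheap improvement. Single-step Bonferroni is a valid rule that Holm dominates in rejections at the same strong family-wise error, under any dependence between the scales.

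Assuming equal effects and 80% single-test power per scale, Holm adds about 7 to 15 points to the chance of confirming both on the article's effective-n t test over correlations from 0 to 0.95. The gain is 9 to 12 points at correlations of 0.5 to 0.8, and reaches about 16 at those correlations only if 6 cluster-level degrees of freedom are assumed. It is 2 to 7.5 points at d = 0.5. Average power per scale rises by half the gain in confirming both, and power for at least one scale does not change. Dominance by Holm does not depend on these assumptions; the size of the gain does.

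**What to change.** Before any results are seen, replace the Bonferroni clause in the Statistical analysis section with wording such as:

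> *The two secondary outcomes (PROMIS-CA, PROMIS-CG) are each tested by the between-arm contrast in pre-post change, using Holm's step-down at family-wise 5% (smaller p at 0.025, then larger p at 0.05).*

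Report ordinary 95% intervals for both contrasts and state that they are not adjusted for multiplicity.

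The cost is one sentence, with no extra data, participants or error rate. What is given up is the simple simultaneous interval that goes with Bonferroni. Because the article says that unblinded investigators will analyse the data, the change should be dated and its reason recorded, so that it cannot be taken for a relaxation made after seeing the p-values.
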